### The intervention

All GPs will audit their consenting patients for dementia, and complete a supplementary audit indicating diagnostic evaluation and management for patients they consider to have dementia. This will occur at three time points during the study: baseline, 12 months and 24 months. Intervention GPs will receive education as described below. The rationale for the educational intervention is described in the *Background *section above.

#### Intervention GPs

Intervention GPs will participate in two visits at their surgery with a peer medical or nurse educator. At the first visit (after completion of the baseline audit), GPs will be taught how to use the GPCOG screening instrument (described below), and will be given information about dementia diagnosis, diagnostic workup and management according to strategies incorporated in the RACGP Consensus Guidelines for the care of Patients with Early Dementia (hereafter called the RACGP Dementia Guidelines) [19]. Negative attitudes about making a dementia diagnosis will be explored and addressed. With the GPs' consent, these sessions will be recorded for qualitative analysis. The structural issue of lack of time in the GP consultation will be addressed by teaching the GPs to use a brief screening instrument and by discussing potential methods of obtaining assistance from the practice nurse. A business case regarding the cost effectiveness of dementia assessment will also be presented. All intervention GPs will be provided with support materials and the RACGP Dementia Guidelines at this visit. These GPs will receive a second detailing visit after completion of their 12 month audit. At the second visit, intervention GPs will receive written and verbal feedback about their baseline audit in the light of individual patient results from the home assessment.

As the study is being conducted across five sites, a number of different peer educators will be used. All educators will undergo a training program either face-to-face or via teleconference to familiarise them with the educational package developed for intervention GPs. The package consists of a slide presentation that will be delivered by educators via laptop computer, and hard-copy support materials that will be supplied to the GPs.

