**Methods:**

The study is a cluster randomised trial, conducted across three states and five sites. All GPs will complete an audit of their consenting patients aged 75 years or more at three time points - baseline, 12 and 24 months. GPs allocated to the intervention group will receive two educational sessions from a peer GP or nurse, and will administer the GPCOG to consenting patients at baseline and 12 months. The first education session will provide information about dementia and the second will provide individualised feedback on audit results. GPs in the waitlist group will receive the RACGP Guidelines by post following the 12 month audit

Outcomes: Primary outcomes are carer and consumer quality of life and depression. Secondary outcomes include: rates of GP identification of dementia compared to a more detailed gold standard assessment conducted in the patient's home; GP identification of differential diagnoses including reversible causes of cognitive impairment; and GP referral to specialists, Alzheimers' Australia and support services. A "case finding" and a "screening" group will be compared and the psychometrics of the GPCOG will be examined.

Sample size: Approximately 2,000 subjects aged 75 years and over will be recruited through approximately 160 GPs, to yield approximately 200 subjects with dementia (reducing to 168 by 24 months).

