#### Waitlist GPs

Waitlist GPs will complete the audits as per Figure 1. No feedback will be given to waitlist GPs during the course of the study. They will be mailed the RACGP Dementia Guidelines after completion of the 12 month audit. Apart from administrative phone calls to obtain the audits, waitlist GPs will have no other contact with the study team.

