### Data collection

#### Patient assessment

The research nurse will use a laptop computer to collect demographic data from all consenting patients and to administer the GPGOG, CAMCOG, GDS, WHOQOL-BREF, GPAQ and ADL (for patients in CAMCOG dementia range only). Patients will be asked about any memory-related services accessed, referral to Alzheimer's Australia, and referral to a specialist for memory problems. The research nurse will compile a list of all prescription and over the counter medications currently used by the patient, so that medication can be excluded as a cause of cognitive impairment. Complementary and alternative medicines will be included. In addition the nurse will perform a "75 + Health Assessment" rebateable under the Australian Medicare system on eligible patients where this has been requested by the GP. These data will not be used by the study, but are returned to the GP for his or her use. This part of the assessment is a provided as a service to the GP. Brief questions used in our previous research will be used to measure the acceptability of the interview process. We will ask patients to send answers back in a reply-paid envelope, to avoid bias due to the presence of the nurse. At the completion of the assessment the nurse will hand the patient a sealed envelope. In the case of patients in the intervention group, it will direct the patient to obtain an appointment with his/her GP as soon as possible to follow up on the 75+ Health Assessment and to have the GPCOG re-administered. In the case of patients in the waitlist group, it will suggest a follow up for the 75 Plus Health Assessment only. Patients will be reassessed using the same instruments at 12 and 24 months after baseline interviews.

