### Outcome measures

Primary outcome measures related to the first aim (collected at baseline, 12 months and 24 months) are:

1. World Health Organization Quality of Life-Bref Scale (WHOQOL-BREF) score for patients

2. Geriatric Depression Scale score for patients

Secondary outcome measures related to the first aim (collected at baseline, 12 months and 24 months) are:

1. World Health Organization Quality of Life-Bref Scale (WHOQOL BREF) for carers

2. Beck Depression Inventory score for carers

3. Agreement of GP audit for dementia with CAMCOG instrument

4. GP differential diagnosis for dementia

5. GP identification and treatment of reversible causes of dementia 6.GP dementia related referrals made

7. General Practice Assessment Questionnaire score

8. Acceptability of the process scale score

9. Services accessed

To meet the second aim of the study, screening and case finding groups (as defined above) will be compared on primary and secondary outcome measures 1 and 2 as listed above. The GPCOG score will be compared with the gold standard of the CAMCOG score to address the third aim of the study. The performance of the GPCOG against the CAMCOG will also be compared with that of the MMSE against the CAMCOG, as the MMSE is widely used to screen for dementia.

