#### Do GPs trained in the use of a screening instrument detect dementia better?

Detection rates of GPs trained in using the GPCOG (the Intervention group) will be compared with detection rates of Waitlist GPs against the 'gold standard' of the CAMCOG.

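### At 24 months the arm comparison of GP detection mixes better detection with feedback of earlier reference results to intervention GPs only

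*Protocol article*

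**What the plan says.** *Timing and content of the feedback.* The Intervention GPs section states: "These GPs will receive a second detailing visit after completion of their 12 month audit". It continues: "At the second visit, intervention GPs will receive written and verbal feedback about their baseline audit in the light of individual patient results", these results coming from the home assessment. For the control arm, the Waitlist GPs section states: "No feedback will be given to waitlist GPs during the course of the study". The dementia guidelines are mailed to waitlist GPs only once their 12-month audit is complete.

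*What the home assessment is.* The abstract describes the outcome as "rates of GP identification of dementia compared to a more detailed gold standard assessment conducted in the patient's home". The Patient assessment section lists the CAMCOG among the instruments that the research nurse gives, and has the same instruments repeated at 12 and 24 months.

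*The outcome.* Under Outcome measures, secondary outcome 3 is "Agreement of GP audit for dementia with CAMCOG instrument". It falls under the lead-in "Secondary outcome measures related to the first aim (collected at baseline, 12 months and 24 months) are".

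*The analysis.* Under Statistical analyses, the first question concerns GP detection. Detection rates of intervention GPs "will be compared with detection rates of Waitlist GPs", with the CAMCOG as reference. The second question compares misclassification rates between arms. Neither question names a time point. The question on health outcomes is placed at twelve months.

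**The concern.** Between the 12- and 24-month audits, one arm is told how individual patients did on the assessment that serves as the reference standard. The other arm is not. Both arms are then asked to classify those patients again and are scored against a repeat of the same instrument. A GP who missed a case at baseline, was told the result, and records dementia at 24 months counts as a detection, although the study supplied the information.

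GP identification of dementia is the first item of the first aim, and GP detection is the first analysis question. If the 24-month figures were read as the answer, a gain could be credited to training in a screening instrument when part or all of it came from passing on results. Misclassification is exposed in the same way, because a GP who wrongly labelled a patient may also be corrected by the feedback.

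**Working it through.** **1. Sequence of events, from the sections cited above**

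| Time | Intervention GPs | Waitlist GPs |
|---|---|---|
| Baseline | Audit, then first visit (GPCOG training, guidelines) | Audit |
| 12 months | Audit | Audit |
| After the 12-month audit | Second visit: feedback on the baseline audit against individual home-assessment results | Guidelines by post; no feedback |
| 24 months | Audit, scored against a repeat CAMCOG | Audit, scored against a repeat CAMCOG |

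The 12-month audit precedes both the feedback and the mailing. The 24-month audit follows both.

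**2. How many 24-month cases had an earlier result to feed back**

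The article's own attrition figures (Study drop outs/withdrawals) reproduce:
- 2,000 × 0.10 = 200 with dementia at baseline
- 200 × 0.9 = 180 at 12 months
- 180 × 0.9 = 162 at 24 months

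The abstract gives 168 at 24 months; the difference does not matter here. The 162 are all baseline cases, and the article expects only a small number of incident cases besides. Let p be the share of 24-month cases already in the dementia range at the assessment fed back. If the 162 all stay in that range, the number of incident cases implied is 162 × (1 − p)/p:
- p = 0.95: about 9
- p = 0.85: about 29

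So 0.85 to 0.95 is compatible with the article's description, but it remains an assumption.

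**3. Apparent sensitivity at 24 months with no true difference in detection**

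Let s be the true detection rate in both arms and q the probability that a GP adopts a disclosed positive result for a missed case. The article gives neither. Then:

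apparent sensitivity (intervention) = s + (1 − s) × q × p; waitlist = s.

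| s | q | p | Intervention | Waitlist | Spurious gain |
|---|---|---|---|---|---|
| 0.5 | 0.5 | 0.85 | 0.5 + 0.5 × 0.5 × 0.85 = 0.71 | 0.50 | 21 points |
| 0.5 | 0.5 | 0.95 | 0.5 + 0.5 × 0.5 × 0.95 = 0.74 | 0.50 | 24 points |
| 0.5 | 0.25 | 0.90 | 0.5 + 0.5 × 0.25 × 0.90 = 0.61 | 0.50 | 11 points |
| 0.7 | 0.25 | 0.90 | 0.7 + 0.3 × 0.25 × 0.90 = 0.77 | 0.70 | 7 points |
| 0.3 | 1.0 | 1.0 | 0.3 + 0.7 × 1.0 × 1.0 = 1.00 | 0.30 | 70 points |

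The last two rows are the extremes of a grid with s from 0.3 to 0.7, q from 0.25 to 1.0 and p from 0.9 to 1.0.

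**4. Chance that such a gain reaches significance**

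This uses the planned 56 waitlist and 112 intervention patients with dementia, two-sided 5%, and a design effect of 1 + (5 − 1) × 0.05 = 1.20. That design effect follows from the article's intra-class correlation and cluster size; the article prints 1.45, which is a separate matter. Effective numbers are 56/1.20 = 46.7 and 112/1.20 = 93.3. The chance is about 0.75 at s = 0.5, q = 0.5, p = 0.9. Over the grid it runs from 0.14 to nearly 1.

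**5. Overall agreement moves less than sensitivity**

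At the article's prevalence of about 10%, a gain of 21 to 24 points among cases adds only 0.10 × 0.21 to 0.10 × 0.24, about 2 percentage points, to raw agreement over all patients. Corrected false-positive labels would add to this; nothing in the article allows that part to be sized.

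**6. The 12-month audit**

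On the timing in the Intervention GPs section, no result has been disclosed by then. So q = 0, and the apparent difference equals the true difference.

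**The case against.** The strongest reply is that feedback is not a leak. The rationale for the intervention and the Study Design section both name audit with feedback as a component, and the first aim refers to the intervention as described. A 24-month arm difference is therefore a proper randomised effect of the package. This stands. What remains is that the package effect answers a different question from the one on detection by GPs trained in a screening instrument.

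Secondly, the 24-month CAMCOG is a fresh assessment, the feedback concerns the baseline audit, status can change, incident cases occur, and GPs need not accept what they are told. This also stands. A reader might infer that 24-month agreement measures nothing but disclosure, or that the intervention is favoured by construction. The article does not support that; it supports only that the two effects cannot be separated at 24 months.

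Thirdly, the detection question does not say that it will be judged at 24 months, and a condensed article may leave the time point to a fuller document. The silence alone is not a fault, and a reader should not infer that 24 months is the intended decisive time. The point rests on what the article does fix: feedback in one arm, its timing, and collection of the outcome at 24 months.

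Finally, the illustrated sizes depend on assumed inputs, and at the low end the distortion is small and unlikely to reach significance. That is correct, and the range is shown for this reason.

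**Conclusion.** The point holds in a limited form. Any arm difference at 24 months in agreement, detection or misclassification mixes better detection with knowledge of earlier reference results that only intervention GPs were given. It may be reported as an effect of the package, but not as evidence that trained GPs detect dementia better.

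The direction for sensitivity follows from the design as long as some GPs act on disclosed positive results. The size does not: the calculations assume detection, adoption and persistence rates that the article does not give.

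The reach is also limited. A reader might infer that the trial's main result is compromised, but the primary outcomes (patient WHOQOL-BREF and GDS) are not scored from GP audits. The 12-month detection comparison is unaffected by the second visit as described. One loose end bears on that: the Study Design section speaks of feedback with all three audits in the intervention arm and does not say when it is given, whereas the Intervention GPs section places feedback on the baseline audit at the second visit.

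**What to change.** 1. In Outcome measures (secondary outcome 3) and in the analysis questions on detection and on differential diagnosis, make the 12-month audit the time point for the arm comparison of GP detection and misclassification.
2. Keep the 24-month comparison, labelled as the effect of the package including feedback of individual results.
3. Treat any 24-month analysis of incident cases as exploratory only. It would be small. It is also open to bias in the other direction, because the feedback is not limited to positive results: a GP told that a patient tested negative may be slower to record a new dementia.
4. Reconcile the Study Design wording on feedback with the Intervention GPs section, so that it is clear that no individual results reach GPs before the 12-month audit.

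The cost is wording only; randomisation, visits and data collection do not change. The price is that the 24-month detection result is no longer used as evidence of better detection.

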#### Waitlist GPs

Waitlist GPs will complete the audits as per Figure 1. No feedback will be given to waitlist GPs during the course of the study. They will be mailed the RACGP Dementia Guidelines after completion of the 12 month audit. Apart from administrative phone calls to obtain the audits, waitlist GPs will have no other contact with the study team.

### Research instruments

The following instruments will be used be used as part of the patient and/or carer assessments:

#### The GPCOG

The GPCOG [18,28] is a simple dementia-screening instrument, translated into a number of languages and is freely available on the internet http://www.gpcog.com.au. The refined version of the GPCOG has not been trialed in a large random sample of GP patients. It is considered superior to other screening instruments such as the MMSE [29] because of its brevity, psychometric properties and its use of informant report in borderline cases [28].

#### The CAMCOG

The CAMCOG is a subsection of the CAMDEX instrument, which has been validated in the UK [30]. The CAMCOG has the MMSE embedded in it and, thus, allows comparison between the GPCOG and the MMSE. The CAMCOG was used in our previous study to validate the original version of the GPCOG [18].

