### Sample size

It was calculated that 45 patients with dementia in each group (Waitlist and Intervention) would give a power of 0.9 to detect a 7% difference between the change in pre and post scores on any of the four domain scales of the WHOQOL-BREF with a type 1 error of .05. The population standard deviation used is 18.5 [32] and the Pearson correlation coefficient between the pre and post scores for both groups is assumed to be 0.7, based on pilot data available from the University of Melbourne.

The hierarchical nature of the study design will probably lead to some within cluster correlations and the greatest impact of this is likely to be associated with patients clustered within a GP practice. Clustering within each GP may be discounted, as it is anticipated that most GPs will have less than five patients with dementia in this study. Assuming an intra-class correlation coefficient of 0.05 and an average cluster size of 5 patients with dementia in a practice, this gives a design effect of 1.45 and a total sample size of 54 patients per group. We will therefore allow for 56 patients with dementia in the waitlist group and 112 in the intervention group to allow for comparison of outcomes between the waitlist and intervention groups overall. This sample size also allows comparison of "case finding" and "screening" patients and their support persons within the group. It is assumed that about 50% of participants will be screening and 50% case finding. Thus, we aim to recruit 168 participants with dementia overall. Based on a dementia prevalence of approximately 10% in over 75 year old Australians [37], we aim to recruit a total of 2,000 participants.

For the GDS, following the same set of assumptions and approach as for the WHO QOL-BREF (power, type 1 error and correlations), 45 patients in both the Intervention and Waitlist groups would allow detection of an average difference in the change in pre and post scores of 0.9 points on the 15 point GDS, using a standard deviation of 2.39 [28]. The cluster effect would be the same as for the WHOQOL-BREF.

For an estimate of test re-test reliability on the GPCOG a sample size of 100 will be used to ensure the correlation is estimated to a reasonable precision. The 95% confidence interval for a Pearson correlation of 0.9 would be [0.86, 0.93] and for a correlation of 0.80 [0.73, 0.85].

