#### Test parameters of the GPCOG

The GPCOG will be compared with the DSM diagnosis derived from the CAMCOG as a 'gold standard', and sensitivity, specificity, positive predictive value, negative predictive value and misclassification rate will be calculated. ROC curve analysis will be employed to examine the discrimination ability of the GPCOG test (i.e. ability to detect dementia) relative to MMSE. This is important as the MMSE is now commonly used in General Practice. GPCOG test-re-test and inter-rater reliability (between the nurse and the GP) will be calculated, using the kappa coefficient and intra-class correlation coefficient.

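### The GPCOG and the MMSE are compared against a CAMCOG reference that contains the MMSE, which tilts the comparison towards the MMSE by an amount the document does not let us calculate

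*Protocol article*

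**What the plan says.** The relevant statements are spread over four sections of the protocol article.

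- **The CAMCOG** (research instruments): "The CAMCOG has the MMSE embedded in it and, thus, allows comparison between the GPCOG and the MMSE".
- **Outcome measures**: for the third aim, "The GPCOG score will be compared with the gold standard of the CAMCOG score to address the third aim of the study". The same section adds: "The performance of the GPCOG against the CAMCOG will also be compared with that of the MMSE against the CAMCOG".
- **Test parameters of the GPCOG**: "The GPCOG will be compared with the DSM diagnosis derived from the CAMCOG as a 'gold standard", and then "ROC curve analysis will be employed to examine the discrimination ability of the GPCOG test (i.e. ability to detect dementia) relative to MMSE".
- **Patient assessment**: the research nurse is "to administer the GPGOG, CAMCOG, GDS, WHOQOL-BREF, GPAQ and ADL (for patients in CAMCOG dementia range only"). The GPCOG is listed in its own right. The MMSE is not listed, so its score comes out of the CAMCOG administration.

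No CAMCOG score without the MMSE items, diagnosis made independently of the CAMCOG, or other safeguard is described for this comparison.

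**The concern.** When a reference standard contains one of the tests it is meant to judge, that test agrees partly with itself. This is incorporation bias. Here it is one-sided, because the MMSE sits inside the reference and nothing in the document suggests that the GPCOG does.

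What is at stake is the comparison with the MMSE named in the third aim. The section on test parameters calls it important because the MMSE is now common in general practice. The section on the GPCOG says that the refined version has not been trialled in a large random sample of GP patients, so readers are likely to give this result weight. A GPCOG that is as good as the MMSE could look worse, and a somewhat better one could lose part or all of its lead.

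**Working it through.** The document gives no AUC, AUC difference or sample size for this comparison, so there is no figure of the plan to reproduce. The check covers the direction of the bias first, then its possible size.

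**Inputs from the document.** The MMSE is part of the CAMCOG. Both tests are judged against the CAMCOG or a diagnosis derived from it. The GPCOG is a separate instrument given in the same nurse assessment. Prevalence is about 10% (Sample size).

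**Inputs that are assumptions.** The document gives none of these:
- *w*, the share of the CAMCOG score carried by MMSE items: 0.1 to 0.3.
- Reliability *r*, the same for both tests: 0.6 to 0.8.
- *f*, the share of test error common to everything done in the session (fatigue, illness, rater): 0 or 0.5.
- Own error variance of the remaining CAMCOG items: 0.25, which is reliability 0.8 when *f* = 0.

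**Model.** True cognition T has variance 1. MMSE = T + e_M and GPCOG = T + e_G, each with error variance σ² = (1 − r)/r, of which a share *f* is the common session effect. The remaining items are O = T + the same session effect + their own error. The reference score is C = w·MMSE + (1 − w)·O, and the lowest 10% on C are cases.

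**Direction.** The covariance of each test's error with the error in the reference is:
- MMSE: wσ² + (1 − w)fσ²
- GPCOG: wfσ² + (1 − w)fσ² = fσ²
- Difference: w(1 − f)σ²

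The difference is positive whenever w > 0 and f < 1. A shared session effect shrinks it but does not reverse it.

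**One case worked through** (r = 0.7, w = 0.3, f = 0):
- σ² = 0.3/0.7 = 0.429, so the SD of each test is √1.429 = 1.195.
- Var(C) = 1 + 0.09 × 0.429 + 0.49 × 0.25 = 1.161, so SD(C) = 1.078.
- Correlation of the MMSE with C: (1 + 0.3 × 0.429)/(1.195 × 1.078) = 0.876.
- Correlation of the GPCOG with C: 1/(1.195 × 1.078) = 0.776.
- With the MMSE items left out (C = O, SD = √1.25 = 1.118), both are 1/(1.195 × 1.118) = 0.748.

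In simulation the same case gives an AUC of 0.952 for the MMSE and 0.909 for the GPCOG, although both have 0.936 against true status.

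**Size.** Spurious AUC gap in favour of the MMSE for two equally accurate tests, from simulations of at least 400,000 subjects:

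| r | f | w = 0.1 | w = 0.2 | w = 0.3 |
|---|---|---|---|---|
| 0.6 | 0 | 0.022 | 0.045 | 0.067 |
| 0.7 | 0 | 0.015 | 0.030 | 0.044 |
| 0.8 | 0 | 0.009 | 0.018 | 0.027 |
| 0.6 | 0.5 | 0.010 | 0.018 | 0.027 |
| 0.7 | 0.5 | 0.007 | 0.013 | 0.019 |
| 0.8 | 0.5 | 0.004 | 0.008 | 0.012 |

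Repeat runs of the largest cell gave 0.064 to 0.067, so the range is roughly 0.004 to 0.065. At w = 0 the gap is zero within simulation error. That follows by construction from giving both tests equal error.

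**If the GPCOG is truly better** (r = 0.7 against 0.6, true AUC 0.936 against 0.908, f = 0): at w = 0.1 it still leads, 0.901 to 0.897. At w = 0.2 the order is reversed, 0.904 to 0.922.

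**The case against.** **The ROC section names a DSM diagnosis, not a bare score.** This is correct, and how that diagnosis is made is not set out in this condensed article. ADL data are collected for patients in the CAMCOG dementia range, but the document does not say whether they enter the diagnosis. If outside information does enter, the bias is diluted. With half the error shared and half the reference coming from non-cognitive information (both assumed), the gap at w = 0.2 to 0.3 falls to about 0.005 to 0.016. It does not vanish, because the diagnosis is still derived from the CAMCOG, and the section on outcome measures names the CAMCOG score itself.

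**The nurse gives the GPCOG and the CAMCOG in the same assessment.** Bad-day effects therefore reach the GPCOG and the reference alike, and only error specific to the MMSE items is peculiar to the MMSE. This stands, and it is why the lower half of the table belongs in the range. The article does not say whether the nurse's or the GP's later GPCOG enters the ROC analysis. With the later one, less error would be shared with the reference.

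**Stronger readings that a reader might infer.** One is that the gap is known to be several hundredths of AUC. Another is that the trial will wrongly favour the MMSE. The document supports neither: it gives no item weight, reliability or error structure, and the third aim states no superiority or non-inferiority hypothesis and no decision rule. A finding that the GPCOG is as good or better would, if anything, be conservative. The reversal shown above rests on independent errors and an assumed true difference.

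It might also be inferred that the main trial results are compromised. They are not. The WHOQOL-BREF and GDS do not involve this reference, and the comparison of GP detection sets two randomised groups against one common reference, with the MMSE not among the tests compared.

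**Conclusion.** The concern holds as a bias of known direction and unknown size in one analysis under the third aim. As fixed in the document, the comparison favours the MMSE as long as its items count in the reference and some of its error is specific to it. The direction also assumes that the GPCOG shares less content and error with the CAMCOG than the MMSE does, and no such overlap is described for the GPCOG. A spurious AUC gap of roughly 0.004 to 0.065 is an illustration under the stated assumptions, not an estimate for this trial, and the true figure may lie below 0.02. The upper part of the range would be enough to mislead a head-to-head comparison, and the remedy needs no new patient contact, so the change is worth making.

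**What to change.** For the GPCOG-versus-MMSE comparison only:

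1. Prespecify a paired AUC comparison of the two tests against a CAMCOG score recalculated without its MMSE items, with the cut-off set to give the same proportion positive as the stated reference.
2. Report it beside the analysis against the stated reference, not in place of it.
3. State that no conclusion in favour of the MMSE will be drawn from the stated-reference analysis alone.
4. Reword the section on the CAMCOG so that it says the embedding favours the MMSE, rather than only that it permits the comparison.

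The cost is rescoring, provided that item-level responses from the laptop interviews are kept, which the article does not state. There are two drawbacks. The cut-off without the MMSE items is matched on the proportion positive and is not an established one. Removing the items also removes the cognitive content they measure, which may disadvantage the MMSE. That is the reason to show both analyses instead of making the reduced score the sole reference.
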